## Results

### Preliminary Findings

A first draft of the serious game was created with funding obtained in March 2024 (Innovation Prize of University Hospitals).

As of May 2025, it was tested in 1 middle school in Réunion Island across all seventh grades, with the approval of the school director and teachers, before the vaccination campaign. The game is intended to be used by teachers alone, without the help of a game animator, to enhance reproducibility.

Children were engaged by the game, and their intention to vaccinate was higher than in other schools. Among the 189 students in seventh grade at that school, vaccination teams had initially received consent for 10 students to be vaccinated. After the intervention/serious game, more students submitted signed consents, and a total of 25 (13.2%) students were vaccinated. In other schools in Réunion during that campaign, vaccination coverage did not exceed 7% (986/14,500, 6.8%).

Although the serious game has been developed, some minor changes need to be considered following this first experience with children. Once finalized, production of several copies will be launched. As registrations are in progress, the study is expected to start during the academic year in August 2026.

### Expected Outcomes

Réunion Island has one of the lowest vaccination coverage rates among regions in France and Europe (14.8% overall, with 16.1% among girls and 3.4% among boys). Within 1 year, we expect this coverage to remain stable or only slightly increase. We hypothesize that by the end of the school year, 30% of children in the control group will have initiated vaccination—based on data published by Santé Publique France in 2023, which reported that 21.5% of 12-year-old children (girls and boys combined) in Réunion had received at least one dose of the HPV vaccine by December 31, 2023.

With this study protocol, we aim to achieve a vaccination coverage rate of around 45% among children through the proposed interventions (ambassador classes and serious games). This target was used to calculate the sample size. It is not yet known which of the 2 strategies will be more effective.

This study protocol could be implemented in other departments. By validating innovative strategies to improve HPV vaccination coverage in middle schools, this research could not only influence national vaccination campaigns but also provide insights for similar initiatives in other medical fields. It could play a central role in combating vaccine hesitancy, particularly among younger generations, by informing the population. The study results may also positively impact the involvement of children and families in vaccination campaigns. By reinforcing messages delivered by health care professionals and improving communication with families of participating children, this study could support greater acceptance of the HPV vaccine, thereby reducing the incidence of benign, precancerous, and cancerous conditions associated with the virus.

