## Introduction

Human papillomavirus (HPV) is a widespread sexually transmitted infection that affects more than 1 in 5 people globally [1]. It is estimated that about 80% of men and women will be exposed to HPV at some point in their lives. With a global prevalence of 31% in men and 32.1% in women [2,3], HPV represents a major public health concern due to its established role in the development of multiple cancers [4], most notably cervical cancer, which remains the fourth most frequent cancer in women worldwide. The World Health Organization reported 660,000 new cervical cancer cases and 350,000 related deaths in 2022. In France, HPV is responsible for over 6400 cancers annually, including cervical, vulvar, vaginal, penile, anal, and oropharyngeal cancers. On Réunion Island, cervical cancer is the third most common cancer in women.

Prevention of cervical cancer is mainly based on screening with Papanicolaou (Pap) smear tests and HPV vaccination. Despite the proven safety and effectiveness of HPV vaccines in reducing the incidence of precancerous lesions and genital warts [5-7], vaccination coverage in France remains insufficient. As of 2023, only 45% of girls and 16% of boys aged 16 were vaccinated [8]. In Réunion Island, coverage is even lower: in 2022, only 12.7% of adolescents under 16 had received at least one dose of the HPV vaccine. Following the national vaccination campaign launched in 2023, only 6.8% of seventh-grade students were vaccinated at school in Réunion. Taking into account children vaccinated outside school by their general practitioner, the rate modestly increased to 27% for girls and 16% for boys. Nevertheless, these figures remain far from the thresholds needed to achieve herd immunity and effective cancer prevention [9].

The low uptake in Réunion Island may be attributed to a lack of information, fear of adverse events, and limited engagement from both health care professionals and families [10,11]. In countries such as Australia, Belgium, Portugal, and the United Kingdom, school-based HPV vaccination programs have achieved coverage rates exceeding 80% [12]. These programs reduce access barriers, promote equity, and provide opportunities for engaging educational interventions.

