**Figure 2 figure2:**
[figure not shown]
Diagram showing the composition of colleges randomly assigned.

To calculate the required number of participants, the following assumptions are considered:

It is hypothesized that, by the end of the school year, 30% of students in the control group will have initiated vaccination. This estimate is based on vaccination coverage data published by Santé Publique France in 2023, which reported that 21.5% of children (girls and boys combined) aged 12 in Réunion had received at least one dose of the HPV vaccine by December 31, 2023 [23].It is hypothesized that the ambassador classes and the serious game will increase coverage to 45% in the respective intervention groups.A constant intracluster correlation coefficient of 0.1, considered a rather conservative value [24].An α risk of 5%90% powerThe average number of seventh-grade students (n) is 190 per college.A design effect (allowing intraclass correlation [ICC] to be taken into account) of 19.9, which is calculated as 1 + ICC × (n – 1).

Therefore, a total of 8 colleges per arm will be included, resulting in 24 colleges overall and approximately 3144 students.

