### Intervention

#### Control Group

The control group will consist of 8 randomly assigned middle schools. These schools will follow the existing vaccination campaign, without any modifications, as implemented by the French government. As vaccination campaigns are coordinated by the local Regional Health Agency, they are relatively uniform across all middle schools in Réunion, ensuring standardization and internal validity. Parents will receive information materials and consent forms through their children. Both parents are invited to sign the written consent form, which the child will then submit to the school counselor or school nurse. The counselor or nurse will forward the forms to the vaccination teams assigned to the area. This allows the vaccination teams, in coordination with the education staff, to schedule their visit to the school on a specific day and bring the appropriate number of vaccine doses corresponding to the consent forms received. Vaccination teams typically visit each school twice a year to administer 2 vaccine doses 6 months apart, usually in December (year Y) and June (year Y+1).

A preintervention questionnaire will be administered to assess students’ baseline knowledge about HPV (T0). The questionnaire will be standardized, anonymous, and identical for all participants. It will be available on tablets, computers, or on paper, depending on availability. A postintervention knowledge assessment will be conducted 3 months later (T1) using a questionnaire identical to the preintervention one, to evaluate changes in the rate of correct responses before and after the vaccination campaign.

The standardized knowledge questionnaire was developed by the research team and will assess students’ knowledge of HPV epidemiology, complications, and prevention (including vaccination; Multimedia Appendix 1). Each question requires a response of “yes,” “no,” or “I don’t know.” The questionnaire consists of 11 questions.

Vaccination status will be collected using the French social security system after anonymization of social security numbers (T3).

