### Study Limitations

Vaccination coverage is expected to continue increasing between 2023 and 2025, which may influence the number of schools included in each study arm and affect the calculation of the required sample size. This trend could potentially reduce the study’s statistical power.

The potential for cross-talk between students in the intervention and control groups may introduce bias in this open/unblinded study and lead to contamination between students, especially in a setting like Réunion Island, where communities can be tightly knit and students may interact across schools or through extracurricular activities.

Interventions cannot be staggered over time because they depend on the academic calendar, which is punctuated by school holidays.

Nevertheless, to minimize contamination between the groups:

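### The 30% control rate behind the sample size is not derived from its 21.5% source, is not reconciled with the protocol's coverage trends, and does not give 90% power with 8 colleges per arm

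*Protocol article*

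**What the plan says.** The control arm is the existing campaign: "These schools will follow the existing vaccination campaign, without any modifications, as implemented by the French government" (Intervention, Control Group).

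The assumptions in the Sample Size section, listed below Figure 2, put the control rate at the end of the school year at 30%. The only basis given is that "21.5% of children (girls and boys combined) aged 12 in Réunion had received at least one dose of the HPV vaccine" by 31 December 2023. The two interventions are assumed to "increase coverage to 45% in the respective intervention groups". The other inputs are an ICC of 0.1, alpha 5%, 90% power, 190 students per college and a design effect of 19.9. The result is 8 colleges per arm, 24 colleges and about 3144 students.

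Expected Outcomes gives regional coverage as "14.8% overall, with 16.1% among girls and 3.4% among boys", with no age group or date, and adds "Within 1 year, we expect this coverage to remain stable or only slightly increase". The next sentence repeats the 30% control rate and its 21.5% source. The section then says that the 45% target was used to calculate the sample size.

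Study Limitations says "Vaccination coverage is expected to continue increasing between 2023 and 2025" and warns that this could affect the sample-size calculation and reduce power. Preliminary Findings puts the start at August 2026, so vaccination status would be read around July 2027.

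**The concern.** The control rate is the least secure input to the sample size, and the text gives three cues about it that are never brought together: a static regional figure, a rising trend that stops at 2025, and a dated source 8.5 points below the assumed value. Nothing explains how 21.5% becomes 30%.

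Because the target is an absolute 45%, each point of change in the control rate changes the planned contrast by one point. At 30% the contrast is 15 points (odds ratio 1.91); at 21.5% it is 23.5 points (odds ratio 2.99); at an assumed 35% it is 10 points. At stake is the stated 90% power, on which the choice of 8 colleges per arm rests.

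**Working it through.** **Inputs.** From Sample Size: control rate p0 = 0.30, source rate 0.215, target p1 = 0.45, ICC 0.1, m = 190 students per college, k = 8 colleges per arm, alpha 0.05, power 0.90. From Statistical Analysis: two-sided testing. The 35% control rate is an assumption, used to represent the rising trend in Study Limitations.

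**1. The plan's own figure.** The design effect is 1 + 0.1 × 189 = 19.9, as printed. The pooled two-proportion formula for 30% vs 45% at 90% power gives 217 students per arm before clustering. Then 217 × 19.9 = 4318 per arm, and 4318 / 190 = 22.7, so 23 colleges per arm. The unpooled formula gives 213.7 × 19.9 / 190 = 22.4, also 23. The printed 8 per arm is not reproduced.

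**2. What does fit.** The unpooled formula for 21.5% vs 45% at 90% power is

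n = (0.215 × 0.785 + 0.45 × 0.55) × (1.960 + 1.282)² / 0.235² = 79.2 per arm.

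Then 79.2 × 19.9 / 190 = 8.3 colleges per arm, and 2 × 79 × 19.9 = 3144, the printed total, for two arms and not three. The match is not unique: the pooled formula with 21% vs 45% also gives 79, while the pooled formula with 21.5% gives 83 (a two-arm total of 3303).

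**3. Power of 8 colleges per arm.** The effective size per arm is 8 × 190 / 19.9 = 76.4. The standard error is √{[p0(1 − p0) + p1(1 − p1)] / 76.4}, and power is Φ(|p1 − p0| / SE − 1.96). The figures in brackets use the noncentral t with 14 df. For 30% vs 45%: SE = √(0.4575 / 76.4) = 0.0774, ratio 0.15 / 0.0774 = 1.94, power 49%.

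| Control rate | 45% held | 15-point gain held | Odds ratio 1.91 held |
|---|---|---|---|
| 21.5% | 89% (84%) | 54% (49%) | 43% (38%) |
| 30% | 49% (44%) | 49% (44%) | 49% (44%) |
| 35% (assumed) | 24% (22%) | – | – |

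The result hardly depends on cluster size. With 3144 / 24 = 131 students per college, the 45% column is 88% at 21.5% and 48% at 30%.

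**4. The regional figures.** For 14.8% overall to follow from 16.1% of girls and 3.4% of boys, the share of girls would have to be (14.8 − 3.4) / (16.1 − 3.4) = 11.4 / 12.7 = 0.90. Equal numbers would give 9.75%. By contrast, the Introduction's post-campaign rates ("the rate modestly increased to 27% for girls and 16% for boys") average (27 + 16) / 2 = 21.5%, which agrees with the sizing source.

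**5. Is 30% reachable?** From 31 December 2023 to about July 2027 is roughly 3.5 years, and 8.5 / 3.5 = 2.4 points a year.

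**The case against.** A reader might infer that the protocol flatly contradicts itself, by expecting stable coverage and then assuming 30%. The text does not support that. The sentence about stability refers to the undated 14.8% regional figure over one year, and not to the 21.5% among 12-year-olds. A rise of 2.4 points a year fits the trend in Study Limitations. The source date also falls mid school year, whereas the outcome is read after the June campaign, when first doses can still be given. Study Limitations itself discloses that rising coverage could cost power. What remains is that the step is not stated and the three sections are not aligned.

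A reader might also infer that power moves by tens of points however the effect is defined. It does so only with 45% held fixed. Between 21.5% and 30% the change is about 5 or 6 points if the 15-point gain or the odds ratio is held. The fixed-target column is still the relevant one, because Expected Outcomes names 45% as the target used for sizing. The direction is not all adverse: if control stays low and 45% is reached, power is higher than at 30%.

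Nor does an uncertain control rate make a null result uninterpretable, or make the trial's verdict depend on reaching 45%. Study Limitations specifies a mixed logistic model comparing each intervention with control, and a null result would be read from the estimate and its interval.

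Finally, the low power at 30% vs 45% is at root a failure of the sample-size arithmetic. That is fair, and the two corrections belong together. But the arithmetic cannot be corrected without first settling the control rate.

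**Conclusion.** The point stands as an unexplained and unreconciled input that does not fit the printed size. On the stated 30% vs 45%, 8 colleges per arm give about 49% power per comparison (44% with t, 14 df) and not 90%; reaching 90% would take about 23. Roughly 90% power with 8 per arm arises only near 21.5% vs 45%. That 21.5% was actually used is inferred from the match with 8 per arm and 3144, and the document does not say so.

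These figures assume the protocol's ICC of 0.1, equal clusters of 190 and unadjusted two-sided 5% for each comparison. The 35% row is an assumption. This should be corrected before the trial starts, because the stated power is a figure that the design relies on.

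**What to change.** - State one control rate under one definition (at least one dose, seventh grade, girls and boys together), for July 2027, with its derivation from 21.5%.
- Make Sample Size, Expected Outcomes and Study Limitations agree on that rate and on the expected trend, with the trend carried through to the actual trial dates.
- Correct the 14.8%, 16.1% and 3.4% figures, giving their age group and date, or remove them.
- Replace the stated 90% with the power that 8 colleges per arm deliver at the chosen rate, and add a short table for control rates from 21.5% to 35%.

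Make this change in the same revision that corrects the sample-size arithmetic, since both alter the same paragraph. The cost is rewording and a small table, with no added schools, students or data. The downside is that the stated power becomes conditional on the control rate and, at 30% or above with 45% as the target, clearly less favourable.

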## Discussion

### Comparison With Previous Work

As mentioned earlier in the introduction, high levels of vaccination coverage are achieved in countries that vaccinate in schools [12]. In 2020, a team in La Réunion increased vaccination rates following interventions, with 26 girls completing the vaccination schedule compared with 3 boys [25].

Peer learning involves students acquiring knowledge or skills through experience, observation, or education [15]. This method allows students to think collectively about a subject, enhancing their critical thinking and understanding. Studies have shown potential benefits of this learning process in clinical training for adults, as well as positive social and academic gains among children. It reduces stress, increases self-confidence, and improves skills [14,26], not only in ambassador students but also among their peers who benefit from the ambassadors’ knowledge [13].

Serious games have been developed as educational tools in recent years. They are immersive games built around a scenario and typically involve solving puzzles within a predetermined time frame. In the health field, serious games were introduced in 2017 to improve knowledge, increase interest and motivation, and enhance team cohesion and communication. However, literature on the subject is scarce, and although participant perception has been evaluated, data on knowledge improvement were not provided [17].

### Study Limitations

Vaccination coverage is expected to continue increasing between 2023 and 2025, which may influence the number of schools included in each study arm and affect the calculation of the required sample size. This trend could potentially reduce the study’s statistical power.

The potential for cross-talk between students in the intervention and control groups may introduce bias in this open/unblinded study and lead to contamination between students, especially in a setting like Réunion Island, where communities can be tightly knit and students may interact across schools or through extracurricular activities.

Interventions cannot be staggered over time because they depend on the academic calendar, which is punctuated by school holidays.

Nevertheless, to minimize contamination between the groups:

We chose to use schools as units of randomization, rather than individual students.We will try to select schools that are geographically separate—ideally from different cities—to limit student interaction, although this remains subject to randomization.We will try to measure the extent of contamination at the end of the study by asking students whether they heard about HPV vaccination from students in other schools.Although blinding is not practically feasible for this study, students and teachers in control schools can be informed that they are part of a general public health campaign without knowing the specific educational strategies tested in other arms. We have planned an objective primary end point to compensate for this. Recovery of vaccination status will be carried out using the French social security system after anonymization of social security numbers.We plan continuous monitoring in the form of visits to establish quality controls throughout the study, including on-site visits and calls to school officials.We will use a mixed logistic model with random intercepts to assess the effect of the 2 interventions, compared with the control group, on the proportion of vaccinated individuals. This model will allow us to account for the cluster structure of the data. By including schools as random effects, we consider that each school may have a different baseline proportion of vaccinated individuals due to unmeasured factors. The interventions will be modeled as fixed effects. A mixed logistic model with a random intercept is an ideal approach for analyzing data in a cluster-randomized study (such as one involving schools) while accounting for contamination bias.

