### Study Objectives

The primary objective is to evaluate the impact of 2 awareness-raising strategies against HPV by involving middle school students to increase vaccination uptake. Specifically, we aim to compare the proportion of students who initiated vaccination before and after the interventions. In addition, we will assess motivations and challenges encountered in both the serious game and ambassador classes, as well as overall student satisfaction and knowledge.

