### Data Collection, Management, and Monitoring

Pre- and postintervention knowledge questionnaires will be identical for all students (Multimedia Appendix 1). Satisfaction questionnaires will be tailored to the specific trial arm—ambassador class or serious game—to evaluate the unique aspects of each intervention (Multimedia Appendices 2 and 3). Data collection via questionnaires will be anonymized and conducted at the class level.

Vaccination status will be collected with the assistance of the French social security system, following anonymization of social security numbers.

All information required by the protocol must be recorded in the observation notebooks, and any missing data must be explained. Data should be collected as they are obtained and transcribed neatly and legibly. Data will be entered into an electronic observation notebook (electronic case report form) using Ennov Clinical software.

A clinical research associate appointed by the sponsor will regularly visit the investigator center—at study initiation, periodically during the research depending on the inclusion rate, and at study completion. During these visits, and in accordance with the risk-based monitoring plan (considering participants, logistics, impact, and resources), the following elements will be reviewed:

Nonopposition from participantsCompliance with the research protocol and defined proceduresQuality of data collected in the observation notebook, including accuracy, completeness, and consistency with source documents (eg, medical records, appointment books, original laboratory results)

A written monitoring report will be prepared for each visit.

An audit may be conducted at any time by individuals mandated by the sponsor and independent of the research team. Its purpose is to verify participant safety and rights, ensure compliance with applicable regulations, and assess the reliability of the data.

An inspection may also be ordered by a competent authority (eg, ANSM [Agence nationale de sécurité du médicament et des produits de santé] in France).

Both audits and inspections may be conducted at any stage of the research, from protocol development to publication of results and the handling of data generated during the study.

Investigators agree to comply with the sponsor’s requirements for audits and with the competent authority’s requirements for inspections.

Four follow-up visits will be scheduled (Textbox 2).

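### The stated primary model leaves differences in schools' baseline coverage to the random intercept; one prespecified school-level baseline covariate would probably gain precision, by an amount that depends on a correlation the protocol does not give

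*Protocol article*

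**What the plan says.** The model is set out in the Discussion, under Study Limitations: a mixed logistic regression with schools as random intercepts. On the fixed part the text says "The interventions will be modeled as fixed effects"; no other covariate is named. The reason given for the random intercept is that "we consider that each school may have a different baseline proportion of vaccinated individuals due to unmeasured factors".

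Three other places bear on the baseline:

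- Study Objectives: "we aim to compare the proportion of students who initiated vaccination before and after the interventions".
- Data Collection, Management, and Monitoring: "Vaccination status will be collected with the assistance of the French social security system, following anonymization of social security numbers". The Settings section places this collection once, around July.
- The follow-up visit textbox (end-of-research visit) asks, for each student, for vaccination initiated within the school year. The Primary Outcome section counts at least one dose by the end of the school year, with no start date.

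Trial Design mentions stratification by middle school level and a constrained randomization. It names no coverage variable for either. Statistical Analysis refers to a separate statistical analysis plan, which is not shown.

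**The concern.** The protocol identifies variation in schools' starting coverage as a nuisance and handles it only through the random intercept. That intercept widens the standard error to the right size. It does not take any of the between-school variance out of the arm comparison. A measured covariate that predicts school uptake does.

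This matters more here than in most trials. There are only 8 schools per arm and, on the plan's inputs, nearly all the uncertainty sits between schools, so more students per school would add little. The objective also speaks of a before-and-after comparison, yet the stated model has no before term.

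**Working it through.** **Inputs** (Sample Size section, assumptions after Figure 2). Control: "30% of students in the control group will have initiated vaccination". Interventions: "the ambassador classes and the serious game will increase coverage to 45% in the respective intervention groups". ICC 0.1, 190 students per school, design effect 19.9, 8 schools per arm, alpha 5% (two-sided in Statistical Analysis), 90% power. The stated total of 3144 students implies 3144/24 = 131 per school; the abstract's 3600 implies 150.

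**1. The plan's own figure.**
Individually randomized size per arm: [1.960 × √(2 × 0.375 × 0.625) + 1.282 × √(0.30 × 0.70 + 0.45 × 0.55)]² / 0.15² = 217.
Times 19.9 = about 4318 students, or 4318/190 = 22.7, so 23 schools per arm. The stated 8 does not reproduce. The power figures below therefore start well under 90%; that is a separate and larger problem.

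**2. Where the variance lies.**
Between-school share = 190 × 0.1 / 19.9 = 95%. With 131 per school it is 13.1/14.0 = 94%.

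**3. Unadjusted precision and power.**
Var(difference) = (0.2100 + 0.2475) × 19.9 / (190 × 8) = 0.00599, so SE = 0.0774.
Noncentral t with 24 − 3 = 21 df: power 45.6% (44.9% with 131 per school). The 95% CI half-width is 16.1 points.

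**4. Adjusted power at ICC 0.1.** Let rho be the school-level correlation between baseline and outcome. The documents do not give it. If rho refers to observed school proportions, the SE is multiplied by √(1 − rho²). If it refers to underlying school rates, only the between-school part shrinks and the design effect becomes (1 − ICC) + m × ICC × (1 − rho²). One degree of freedom is spent, leaving 20. The simulations build the baseline from 131 or 190 students, so they include its sampling error.

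| rho | SE × √(1 − rho²), m = 190 | Between part only, m = 190 | Simulation, school proportions, m = 190 | Simulation, logit scale, m = 131 / 190 |
|---|---|---|---|---|
| 0 | 45.4% | 45.4% | 44.6 → 42.7% | not run |
| 0.3 | 49.0% | 48.8% | 44.6 → 46.3% | 45.5 → 45.8% / 46.0 → 47.3% |
| 0.5 | 56.7% | 56.1% | 44.6 → 52.0% | 45.5 → 52.6% / 45.7 → 53.9% |
| 0.7 | 73.3% | 71.5% | 43.9 → 66.4% | 46.3 → 65.7% / 47.6 → 68.1% |

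At rho 0.5 the SE falls to 0.0670 and the CI half-width to 14.0 points. All these calculations work on school-level summaries and approximate the mixed logistic model.

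**5. If the ICC were near 0.03**, roughly where 8 schools would give about 90% power by the normal approximation: with 21 df, power is 87.1% (m = 131) or 89.1% (m = 190). At rho 0.5, shrinking the between part only, it becomes 93.2% or 94.8%, a gain of about 6 points. The logit-scale simulation gives 87.5 → 90.8% and 88.4 → 92.7%, a gain of 3 to 4. Across the methods tried the gain is about 3-7 points.

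**6. Can the source supply the baseline?** To report initiation within the school year for each student, the extract must separate in-year doses from earlier ones, so doses must be dated in some form. The before-and-after objective needs the same information. This is an inference; no section states that dose dates are returned.

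**The case against.** The strongest reply is that nothing here is invalid. A mixed logistic model with a school random intercept is a sound analysis for a cluster trial, and covariates are often settled in the statistical analysis plan. That plan may add one, and the Study Limitations text does not say that the list of fixed effects is complete. This stands as far as it goes. But the article does set out the model's terms and names baseline differences as the reason for the intercept, so this is where the covariate belongs.

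Four stronger readings are tempting, and the documents do not support them:

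- *That the plan calls pre-trial coverage unmeasured.* The sentence applies that word to the factors behind school differences, not to coverage.
- *That the unadjusted analysis is biased by chance imbalance between 8 and 8 schools.* Such imbalance is already reflected in the random-intercept standard error. It costs precision and leaves the test unbiased. The constrained randomization may also limit it, though its variables are not named.
- *That the correlation must be high because "21.5% of children (girls and boys combined) aged 12 in Réunion had received at least one dose", against 30% planned.* That figure is dated 31 December 2023, after the national campaign began and in the month when first school doses are usually given. It is not a pre-September figure. If the endpoint counts only in-year doses, higher baseline coverage leaves fewer students to initiate, and the correlation may be low or negative.
- *That per-school counts exist for the trial schools.* Preliminary Findings gives one pilot school (25 of 189) and a pooled total for the others (986 of 14,500).

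**Conclusion.** The point holds as a recommendation on precision. The stated model leaves about 95% of the contrast's variance untouched when a plausible predictor of it is probably within reach of the planned extract.

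The size rests on an assumed correlation. At ICC 0.1, power goes from about 45% to 46-49% at rho 0.3, 52-57% at 0.5 and 66-73% at 0.7, with a loss of up to about 2 points at zero. With an ICC near 0.03 the gain at rho 0.5 is about 3-7 points. The gain depends on rho squared, so what matters is how far the correlation lies from zero. It is likely to be higher if all doses by the end of the year count (Primary Outcome) and may be low or negative if only in-year doses count (end-of-research visit). Those two passages must be reconciled before the gain can be judged.

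A reader might infer that adjustment rescues the trial's power. At the protocol's ICC it does not: even at rho 0.7, power stays well short of 90%.

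**What to change.** In the model description under Study Limitations, and in the analysis plan, prespecify one school-level fixed effect: the proportion of the school's included seventh-grade students with at least one HPV dose before the start of the school year, taken from dose dates in the same social security extract. Keep the random intercept, and say that it covers the between-school variation left after this adjustment. Report the standardised difference in proportions beside the adjusted odds ratio, and give the unadjusted result as a sensitivity analysis.

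Confirm with the data provider that dose dates are returned. If they are not, the school's count from the previous campaign is a weaker substitute: it describes another cohort and misses doses given outside school, which the Introduction shows to be substantial (6.8% vaccinated at school, against 27% of girls and 16% of boys overall). Use it only if it exists for every trial school.

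State in the same revision whether doses given before the school year count toward the primary outcome.

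The cost is one sentence, one variable in an extract already planned, and one of about 21 between-school degrees of freedom. The odds ratio becomes conditional on the covariate, which the standardised difference handles. No schools, students or staff are added. The study is expected to start in August 2026, so the choice can still be fixed before any outcome is seen.
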